## Abstract

**Supplementary Information:**

The online version contains supplementary material available at 10.1007/s00406-026-02245-7.

## Background

People with severe mental illness (SMI) suffer from mental health problems associated with chronic and persistent challenges that substantially affect functioning across key life domains, including social, occupational, and housing areas, and require long-term intensive support [2, 3]. Most individuals with SMI are diagnosed with psychotic disorders [2]. Other common conditions include bipolar disorder, major depressive disorder, and substance-related disorders. Approximately 1.3% of the Dutch population lives with SMI, with 43% requiring long-term psychiatric care for six years or longer in settings such as sheltered housing or clinical facilities [4]. Individuals with SMI frequently experience persistent symptoms [5], difficulties with medication adherence [6], physical health problems [7], and challenges in self-care [2, 8]. These challenges may extend to daily functioning, such as managing household tasks, using public transportation, or occupational capabilities [9, 10].

Many functional difficulties are highly prevalent [11] and associated with cognitive impairments [12–16], particularly in memory, attention, and executive functioning (e.g., planning and organising) [17–19]. The most common treatment for schizophrenia, antipsychotic drugs, has the potential to reduce positive symptoms but has little beneficial effect on cognitive problems [20]. This has stimulated interest in interventions targeting (the impact of) cognitive impairments directly [21–25]. Recent studies indicate that about 40% of the individuals with schizophrenia achieve full recovery across clinical, functional and personal domains [26–28]. Interventions, particularly targeting cognitive functioning, may further support independence [29], recovery [30], and quality of life [31].

Cognitive remediation (CR) refers to a class of evidence-based behavioural interventions designed to improve cognition and thereby enhance daily functioning [32]. Beyond these gains, CR may also yield broader therapeutic benefits, including improvements in motivation, metacognitive awareness, and self-esteem, as well as alleviation of negative symptoms [33–36]. Meta-analyses demonstrate that CR significantly improves psychosocial functioning in people with schizophrenia [22, 24, 25, 37, 38], particularly when integrated with broader rehabilitation efforts that support real-world generalisation [21, 22]. CR has also shown promise across other diagnostic groups, including mood disorders [39], eating disorders [40], borderline personality disorder [41], and attention deficit hyperactivity disorder [42]. Although some evidence supports its effectiveness among individuals in forms of sheltered or long-term clinical accommodations, the literature remains scarce [43].

Decades of research have identified four core components critical to CR’s effectiveness: trained therapist guidance, strategy learning, repetitive practice, and transfer to daily functioning [23, 25, 44, 45]. The “Computerised Interactive Remediation of Cognition and Thinking Skills” (CIRCuiTS™, King’s College London) is such an intervention that incorporates all these components [44, 46]. This program has demonstrated effectiveness in people with psychotic disorders, but has not yet been applied in people with SMI in sheltered housing. Studying CR in this population is particularly relevant, given their high support needs and additional learning challenges.

Cognitive improvements resulting from CR have been linked to structural changes in the brain essential for retaining newly acquired skills [47], including increased network activation [48], and white and grey matter alterations [49, 50]. The brain’s ability to change and adapt neural connections in response to experiences or learning is called neuroplasticity and plays a critical role in maintaining and improving cognitive functioning and adaptation to new situations [51].

Research suggests that methods such as transcranial direct current stimulation (tDCS) may improve neuroplasticity. TDCS is a non-invasive brain stimulation (NIBS) technique that uses low electrical currents, typically 1–2 mA, and can be applied relatively easily with minimal side effects [52]. By applying electrodes to specific scalp areas, tDCS can selectively modulate brain activity and neocortical excitability in underlying cortical regions [52–54]. It potentially improves cognitive functioning by altering neurotransmission [55, 56] in schizophrenia [57, 58]. Of particular interest is the frontoparietal brain network (FPN), an interconnected brain region important in executing cognitive tasks [59], which is often affected in schizophrenia [60]. Within this network, the left dorsolateral prefrontal cortex (DLPFC) is identified as a key region mediating executive functions and a potential target for tDCS [61].

It has been suggested that combining CR with other methods that improve neuroplasticity, including NIBS, medication, or physical exercise, could result in more significant and longer-lasting improvements and reduce the duration of training protocols [62]. By combining cognitive training with tDCS, improvements in attention and working memory in neuropsychiatric disorders are observed, although effects on global cognition and language remain small and statistically nonsignificant [63]. However, current evidence regarding the effectiveness of combined approaches to improve cognition, particularly CR with NIBS, remains limited. This is mainly due to heterogeneity and methodological weaknesses, such as small group trials and insufficient assessment of real-world generalisation [64]. Moreover, evidence on whether any additive effects of tDCS translate to improvements in everyday functioning remains limited [64]. In a recent meta-analysis, tDCS emerged as the most frequently used NIBS technique in combination with CR [64]. Compared to repetitive transcranial magnetic stimulation (rTMS), tDCS is more cost-effective, portable, better tolerated, and can be applied concurrently with CR. Although tDCS has limited spatial focality, it may modulate distributed prefrontal networks that are relevant for CR. Nevertheless, empirical evidence supporting CR with tDCS augmentation, particularly in inpatient or long-term care settings and for everyday functioning outcomes, remains preliminary and requires further investigation.

We previously demonstrated the feasibility and acceptability of this combined approach in individuals with SMI in a pilot study [65, 66]. In that pilot, preliminary outcome patterns suggested improvements in a global cognition composite after CR and at follow-up, whereas between-group differences (active vs. sham) were not detected. Accordingly, the tDCS augmentation question is prespecified as a secondary and exploratory objective. The rationale for testing this combination in sheltered housing is based on the hypothesis that neuromodulation may support CR, alongside the established feasibility and safety, and substantial unmet clinical need in this population. Building on this work, the current multi-centre clinical trial primarily investigates the effectiveness of a CR intervention in individuals with SMI residing in sheltered housing, while secondarily comparing CR with augmented tDCS.

The primary objective is to assess whether participation in the CR programme leads to improved goal attainment, daily functioning, and cognitive functioning, compared to a waitlist control period in which participants receive treatment as usual (TAU). The second objective is to explore whether combining CR with augmented active tDCS improves the effects of CR combined with sham tDCS, as measured by the same outcome measures. We hypothesise that participants receiving CR will show significantly greater improvements in goal attainment, daily functioning, and cognitive functioning compared to those in the waitlist condition. Furthermore, we expect that the combination of CR with active tDCS will demonstrate significantly greater improvements across the same domains compared to CR with sham tDCS.

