#### Secondary outcome measures

Cognitive outcomes are assessed across multiple domains, with at least one test per MATRICS domain, except for social cognition, which is not targeted in this trial.

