### Statistical analysis

Data analyses will follow an intention-to-treat approach using multilevel models implemented in R (‘lme4’ or ‘glmer’ packages). This approach accounts for the nested structure of repeated measures within participants and participants nested within centres. Model assumptions will be assessed using scatter plots of residuals and Quantile-Quantile (QQ) plots. Multilevel models are generally robust to moderate violations of normality. Models will be estimated using maximum likelihood, which uses all available data under a missing-at-random assumption.

We will build separate multilevel models for each primary and secondary outcome. Timepoint will be included as a categorical within-subject variable with four levels (T0 = baseline; T1 = pre-intervention; T2 = post-intervention; T3 = follow-up). Centre and tDCS condition (active vs. sham) will be included as between-subject variables. Given the staged recruitment, cohort will be included as a fixed-effect covariate to account for cohort-related differences over time (e.g., staff changes or evolving site practices). Models will include a random intercept for baseline differences across individuals, and, where supported, a random slope for timepoint will allow individual trajectories over time (simplified if convergence issues arise). Fixed effects will be estimated for timepoint, tDCS condition, centre, cohort, and their relevant interactions. We will set T1 (pre-intervention) as the reference level to be able to compare T0 vs. T1 (changes during waitlist period), T2 vs. T1 (changes during intervention), and T3 vs. T1 (longer-term changes).

The primary CR effect will be evaluated by comparing changes observed during the intervention period with changes during the waitlist period, pooling across tDCS conditions. The tDCS augmentation hypothesis will be tested via the intervention × timepoint interaction, operationalised as the difference in change from T1 to T2 and from T1 to T3 between active tDCS and sham tDCS. Given the trial is powered for the primary within-subject CR effect rather than the between-group tDCS contrast, tDCS results will be interpreted as secondary and hypothesis-generating, emphasising effect size estimates and 95% confidence intervals.

We have three primary outcomes (GAS, ILSS-O, ILSS-SR). To control multiplicity, we will control the family-wise Type I error rate across the three primary outcomes at two-sided α = 0.05 using the Holm correction.

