## Discussion

The HEADDSET+ study is a pragmatic, randomised, sham-controlled, multi-centre trial evaluating the effectiveness of CR alone and in combination with tDCS in individuals with SMI living in sheltered housing. By targeting goal attainment, daily functioning and cognitive functioning, this study aims to improve independence, recovery, and overall quality of life. CR provides structured cognitive training that supports functional improvements, while tDCS may increase neuroplasticity. TDCS may modestly augment the effects of CR, although current evidence is mixed, and effects appear small [62, 64]. If proven effective, this combined intervention can be integrated into standard care, providing an effective treatment for individuals with SMI requiring long-term support.

This trial builds directly on our earlier pilot study [66] by expanding the sample size, modifying inclusion criteria, and optimising outcomes. The primary outcome, the Goal Attainment Scale (GAS), offers a standardised method to capture progress on personalised goals, typically formulated at the level of cognitive functioning, daily functioning, or participation, thereby ensuring functional relevance and promoting adherence [73]. Our pilot trial showed that participants experienced difficulties setting goals, underscoring the importance of using a structured instrument, such as the GAS, to form goals prior to starting CR, consistent with earlier research [75, 76, 106]. Secondary measures include questionnaires on metacognition and self-efficacy to clarify potential treatment effects, alongside self- and observer-rated questionnaires to provide insight into cross-perspective agreements. Finally, the Behapp smartphone application adds an innovative, objective complement to traditional self-report measures through real-time monitoring of social and daily activities.

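### The primary objective and hypothesis include cognitive functioning, but the confirmatory family of three outcomes contains no cognitive measure

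*Protocol article*

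**What the plan says.** The protocol article describes what is primary in several places.

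- **Background, final paragraph.** The primary objective is whether CR "leads to improved goal attainment, daily functioning, and cognitive functioning" compared with the waitlist period. The hypothesis predicts "significantly greater improvements in goal attainment, daily functioning, and cognitive functioning compared to those in the waitlist condition".
- **Secondary outcome measures.** Cognition is introduced here, not under the primary outcomes: "Cognitive outcomes are assessed across multiple domains, with at least one test per MATRICS domain", apart from social cognition.
- **Statistical analysis.** The confirmatory set is named: "We have three primary outcomes (GAS, ILSS-O, ILSS-SR". (The informant version of the ILSS is labelled ILSS-I elsewhere in the article; I take ILSS-O to be the same measure.) On multiplicity, "we will control the family-wise Type I error rate across the three primary outcomes at two-sided α = 0.05 using the Holm correction". For everything else, "We will build separate multilevel models for each primary and secondary outcome".
- **Discussion.** "The primary outcome, the Goal Attainment Scale (GAS), offers a standardised method", in the singular.

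The Background also reports the pilot results on a global cognition composite. The article does not name such a composite as an outcome of this trial.

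**The concern.** A primary hypothesis with three domains should map onto the tests that can confirm it. Here two domains do and the third does not. A reader of the Background would expect a confirmatory answer on cognition, but the Statistical analysis section provides none.

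If the plan is followed as written, the statement about cognition must come from many separate models. Nothing says which score, or how many, would establish that cognitive functioning improved. A claim presented as part of the primary hypothesis would then lack the error control that the plan gives to the other two parts.

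Timing adds to this. The primary CR contrast is a before-and-after comparison pooled over stimulation arms, so it can be seen without unblinding tDCS. Concealing the tDCS allocation until the last follow-up therefore does not protect the CR claim, and pre-specification is its main safeguard.

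**Working it through.** **1. The plan's own figure.** The plan gives no error rate for cognition. Its one figure that matters here is the sample size (Proposed sample size and power calculation): paired t-test, two-sided α = 0.05, power 0.80, d = 0.36, giving 50 per group, and 126 in total after 20% dropout.

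- Normal approximation: n = ((1.960 + 0.842)/0.36)² = 60.6, so 61 pairs. The exact noncentral-t calculation gives 63 pairs.
- The stated 50 is not reproduced two-sided; it matches a one-sided test (exact n = 50). That is a separate matter.
- Dropout step: 50/0.8 = 62.5, so 63 per group and 126 in total. This reproduces.
- The CR analysis pools both arms, so the planned number of completers is about 126 × 0.8 ≈ 100. I use that below.

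**2. Domains against the confirmatory family.**

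| Domain | In primary objective and hypothesis | In Holm family |
|---|---|---|
| Goal attainment | yes | GAS |
| Daily functioning | yes | both ILSS versions |
| Cognitive functioning | yes | none |

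**3. Number of cognitive scores** (Secondary outcome measures, from processing speed to observed cognitive functioning).

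- Performance scores: COWAT 1, TMT-A and -B 2, Digit Span 2, Visual Reproduction recall and recognition 2, WT-15 immediate and delayed 2, Key Search 1, Stroop interference 1. Sum: 11.
- Rating scores: DEX self and informant 2, CFQ 1, NOSCA 1. Sum: 4.
- Total: 15. Negative symptoms, self-efficacy, social functioning and Behapp are left out.

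**4. Chance of at least one false positive**, if CR has no effect on any cognitive score and each score is tested once, for one contrast, at two-sided 0.05.

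- Independent tests: 1 − 0.95^k. For k = 15, 1 − 0.463 = 0.54. For k = 11, 1 − 0.569 = 0.43.
- Correlated tests: simulation of equicorrelated normal test statistics, 300,000 draws. The documents give no correlations, so these are assumed.

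| Assumed correlation | 15 scores | 11 performance scores |
|---|---|---|
| 0 | 0.54 | 0.43 |
| 0.3 | 0.46 | 0.37 |
| 0.5 | 0.36 | 0.30 |
| 0.7 | 0.26 | 0.22 |

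Counting only errors in the favourable direction, 15 independent tests give 1 − 0.975^15 = 0.32.

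**5. Room for a fourth primary outcome.** Take the strictest Holm step and assume that d = 0.36 also holds for a cognitive composite on the paired-test basis.

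| Family | Level at strictest step | Completers for power 0.80 (exact) | Power at 100 completers |
|---|---|---|---|
| Three outcomes, as planned | 0.05/3 | 84 | 0.88 |
| Four outcomes | 0.05/4 | 90 | 0.85 |

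Ninety completers mean 90/0.8 = 112.5, so 113 recruits, within the planned 126.

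**The case against.** The strongest reply is that the Statistical analysis section already settles what is confirmatory: three named outcomes, Holm at two-sided 0.05, and one CR contrast that sets change over the intervention against change over the waitlist. Cognition is openly labelled secondary. Secondary outcomes need no correction, and their handling, including any composite, is commonly left to an analysis plan, which is not shown here. The Discussion sentence explains why GAS was chosen and sets no testing rule.

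Much of this stands, and it rules out several stronger readings that a reader might infer:

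- **That the confirmatory claim is not fixed, so the headline could follow the result.** The family and contrast are fixed, and the error rate of the three outcomes is unaffected. One loose singular in the Discussion does not displace that.
- **That any one of 15 significant scores would count as success.** No such rule is written. The problem is that no rule is given for a domain named in the primary hypothesis.
- **That sizing the trial on daily functioning contradicts the primary outcomes.** It does not; daily functioning is among them.
- **That the secondary analyses are wrong because they are uncorrected.** The article only states no correction, and that alone would be no fault.
- **That the false-positive chance is simply 54%.** That is the independence figure. Scores from the same person, such as immediate and delayed recall of one word list, will be correlated.

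What the reply does not remove is the mismatch inside the article. An analysis plan could add a composite, but it cannot make the published objective and hypothesis agree with a confirmatory family that leaves cognition out.

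**Conclusion.** The point holds as a mismatch between claim and test: the primary objective and hypothesis cover three domains and the error-controlled family covers two. The false-positive chance for the uncovered domain is between about 0.26 and 0.54 over 15 scores, or 0.22 and 0.43 over the 11 performance scores. These ranges assume no true effect on cognition, one contrast per score, two-sided 0.05 without correction, and correlations between 0.7 and 0. They describe the cognitive claim only and do not touch GAS or the ILSS.

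This should be corrected, because as written a part of the primary hypothesis would be decided outside the stated error control. It does not threaten the validity of the three primary tests.

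**What to change.** Make the Background, Secondary outcome measures, Statistical analysis and Discussion agree, by one of two routes:

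1. Move cognitive functioning out of the primary objective and hypothesis into a secondary objective, assessed on one pre-specified composite of the performance tests, with the individual tests reported as supportive.
2. Keep it in the primary objective and add that one composite to the Holm family as a fourth primary outcome, accepting the small loss of power at the strictest step shown above.

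One workable composite is the mean of z-scores standardised to T0, with signs aligned so that higher is better. Completion times must be reversed. The direction of Key Search needs confirming first: the Executive functioning paragraph describes deductions for slow responses, yet says that higher totals mean worse performance.

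Under either route, change the Discussion to say that GAS is one of the primary outcomes.

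**Cost.** One derived variable from data already being collected, and a logged protocol amendment. Because the trial is registered and ethics-approved, a change to the primary objective or outcome set should also be reported to the registry and the ethics committee. Individual cognitive tests lose any confirmatory reading. With 59 participants enrolled at submission and recruitment ongoing, the change can still be made well before the data are complete.

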## Method

### Trial design

This pragmatic, triple-blinded, randomised, sham-controlled multi-centre trial follows a non-concurrent multiple baseline design (Fig. 1). Recruitment and eligibility assessment are followed by enrolment into five cohorts, each comprising approximately 20–24 participants, spaced 16–20 weeks apart. After inclusion, participants complete two baseline assessments (T0, T1), separated by a 16-week waiting period serving as a within-subject control, offering greater internal validity than a between-subject design. This design enables all participants to receive the intervention and attain its potential benefits. After T1, participants are randomised to either CR + active tDCS or CR + sham tDCS. After the 16-20-week intervention period, outcomes are reassessed post-treatment (T2, within 2 weeks) and at 6-month follow-up (T3).

**Fig. 1 Fig1:**
[figure not shown]
Flowchart of the study design

### Study population

Eligible participants are individuals with SMI defined as follows: (1) having a psychiatric disorder requiring care or treatment (no remission of positive, negative, and cognitive symptoms); (2) severe disabilities in social and societal functioning (no functional remission); (3) disabilities resulting from a psychiatric disorder; (4) disabilities being structural (lasting at least several years); (5) coordinated professional care is necessary to realise a treatment plan [2, 3]. Participants must reside in sheltered housing facilities of a psychiatric institute, where staff provide continuous assistance (24/7) with daily activities when necessary. Additional inclusion criteria are: (1) age 18–65, (2) sufficient written and oral proficiency in Dutch, and (3) ability to provide informed consent. Exclusion criteria are: (1) having previously received CIRCuiTS, (2) contraindications for tDCS (e.g., intracranial metal or electronic implants, severe scalp skin lesions, history of seizures), and (3) substance use interfering with the participant’s typical level of functioning during training sessions.

Eligibility is determined through screening against predefined inclusion and exclusion criteria. Participants also complete a tDCS screening checklist. If any concerns arise (i.e., a ‘yes’ response to any of the questions), the researcher (NB) gathers additional information from the participant and, if needed, their clinician to determine whether it constitutes a contraindication for participation. Remaining uncertainties are discussed with the research team, including tDCS experts and clinicians.

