### Study centres and recruitment

Participants are recruited from sheltered housing facilities at three mental health care organisations in the Northern Netherlands: Cosis, GGZ Friesland, and Lentis Psychiatric Institute. Recruitment involves collaboration with healthcare professionals at these institutes, who help identify potential participants and organise informative meetings. Eligible participants receive detailed oral and written information about the study and have at least one week to decide. Written informed consent is obtained before participation, and participants may direct any further questions to the researchers. Participants are informed about the randomised trial design, emphasising that group assignment is random and that improvement in goal attainment, daily functioning, or cognition cannot be guaranteed. Retention is promoted by maintaining regular contact with participants during the waitlist period, offering flexibility to accommodate participants’ preferences, and emphasising the potential benefits of the training. Withdrawal is possible at any time without consequences.

After completing the training, participants are invited to participate in an additional in-depth interview. They receive the same informed consent procedure and detailed information (i.e., time to consider participation, questions, consent, and withdrawal) only if they express interest. Researchers or CIRCuiTS therapists invite participants during or after the final training session.

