### Interventions

CR and tDCS are delivered individually, twice weekly for 16–20 weeks, equating to 32–40 sessions. Given that missed sessions may occur over this period, intervention completion is defined as attending at least 20 sessions, in line with the developers’ recommendations [44]. Each session lasts 30–45 min, depending on the participant’s attention span, with tDCS applied concomitantly during the first 20 min of CR. Therapists determine the total number of sessions required based on individual progress and needs. Missed sessions are not rescheduled. Before, throughout, and after the study, participants continue to receive treatment as usual, including therapies and activities such as cognitive behavioural therapy, creative therapy, or psychomotor therapy tailored to each individual’s needs.

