### Participant timeline

An overview of enrollment, intervention, and assessments is shown in Table 1.

**Table 1 Tab1:** Schedule of enrolment, interventions, and assessments

Timepoint	Enrolment	Pre-intervention		Intervention	Post-intervention	6-months follow-up
	< T_0_	T_0_	T_1_		T_2_	T_3_
Enrolment						
Eligibility screen	x					
Informed consent	x					
tDCS safety checklist	x					
Randomisation						
Allocation			x			
Interventions						
CR + active tDCS				x		
CR + sham tDCS				x		
Assessments						
PANSS-6		x				
GAS		x (goals set)	x (outcome rated)		x (outcome rated)	x (outcome rated)
ILSS-I & -SR		x	x		x	x
COWAT		x	x		x	x
TMT-A & -B		x	x		x	x
BADS key search		x	x		x	x
WMS-IV visual reproduction		x	x		x	x
Digit Span (forward/backward)		x	x		x	x
WT-15		x	x		x	x
SCWT		x	x		x	x
CFQ		x	x		x	x
DEX-S & -I		x	x		x	x
NOSCA		x	x		x	x
SNS		x	x		x	x
GSES		x	x		x	x
SFS		x	x		x	x
Behapp		x	x		x	x
In-depth interview					x	

*BADS* Behavioural Assessment of the Dysexecutive Syndrome, *CFQ* Cognitive Failure Questionnaire, *COWAT* Controlled Oral Word Association Test, *CR* cognitive remediation, *DEX−S & −I* dysexecutive questionnaire – self & informant, *GAS* Goal Attainment Scale, *GSES* General Self−Efficacy Scale, *ILSS−I & −SR* independent living skills survey – informant & self−report, *NOSCA* nurses’ observational scale of cognitive abilities, *PANSS−6* The Positive and Negative Syndrome Scale – brief, *SCWT* Stroop Colour and Word Test, *SFS* Social Functioning Scale, *SNS* self−evaluation of negative symptoms, *tDCS* transcranial direct current stimulation, *TMT* Trail Making Test, *WMS−IV* Wechsler Memory Scale – Fourth edition, *WT−15* 15−word learning task

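### The tDCS safety checklist is scheduled only before T0, at least 16 weeks before allocation and first stimulation, and no scheduled step re-confirms the tDCS exclusion before randomisation

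*Protocol article*

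**What the plan says.** Under Study population, the second exclusion criterion is "contraindications for tDCS (e.g., intracranial metal or electronic implants, severe scalp skin lesions, history of seizures" and similar conditions. The same section names the tool that enforces it: "Participants also complete a tDCS screening checklist". Any positive answer is followed up by the researcher with the participant and, if needed, the clinician. What remains unclear goes to the research team, including tDCS experts.

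Table 1 (Participant timeline) lists the "tDCS safety checklist" as a row of its own. It has one mark, in the enrolment column before T0. The T1 column holds allocation and the repeated outcome measures.

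Trial design gives the order of events. "Recruitment and eligibility assessment are followed by enrolment into five cohorts". T0 and T1 are then "separated by a 16-week waiting period serving as a within-subject control". "After T1, participants are randomised to either CR + active tDCS or CR + sham tDCS". Stimulation is given within the training sessions, "with tDCS applied concomitantly during the first 20 min of CR".

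**The concern.** An exclusion criterion that protects participants from a device should hold when the device is first used. Here it is checked at entry to a long wait, and the device is used after the wait. All three examples in the criterion can arise in that time: a first seizure, a scalp lesion or a new implant. No scheduled step stands between such an event and allocation. What is at stake is participant safety: the trial's own safeguard is placed well before the exposure it is meant to guard.

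**Working it through.** No sample-size, power or alpha figure bears on this point. The check sets the schedule against the order of events.

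1. **Time of the check.** Table 1: before T0, once.
2. **Time of allocation.** Trial design and Table 1: at or after T1, which is 16 weeks after T0.
3. **Shortest interval from check to allocation.** (Screening to T0) + (T0 to T1) = (0 or more) + 16 = at least 16 weeks. The time from screening to T0 is not given and can only lengthen this. First stimulation is later than allocation, so the same minimum applies to it.
4. **Interval to the end of stimulation.** Interventions gives a training period of 16 to 20 weeks. For a participant trained over the whole period, that is at least 16 + 16 = 32 to 16 + 20 = 36 weeks after the only scheduled check.
5. **Search for another step that re-confirms the criterion before randomisation.**
   - *Contact during the wait.* Study centres and recruitment describes it as a retention measure: "Retention is promoted by maintaining regular contact with participants during the waitlist period". No eligibility question is attached to it.
   - *The T1 visit.* Under Assessments, test assessors administer the primary and secondary outcomes. Under Randomisation and blinding, those assessors do not know the study's design or purpose, so they cannot be relied on to recognise a new tDCS contraindication.
   - *Allocation.* It is carried out by an independent researcher with no other part in the trial, and no eligibility check is assigned to that role.
   - *Medical history.* Other medical events are collected as baseline data, with no update described.
   - *Session records.* Adverse event reporting has therapists record complaints and side effects at each session. This starts only after allocation.
   - *General adverse event reporting.* Events reported by participants, researchers or health professionals are assessed for seriousness and passed on. A seizure during the wait could enter here, but the stated purpose is reporting, and no link to eligibility is given.
6. **Number affected.** The documents give no incidence of new contraindications. An expected count is 126 × p for an assumed 16-week incidence p. With p = 0.5% it is 0.63, and with p = 5% it is 6.3. The result follows the assumption alone. It also takes all 126 to reach T1 and nothing else to detect a case. No conclusion is drawn from it.
7. **Who could still benefit.** Trial status reports 59 enrolled against a target of 126, so 126 − 59 = 67 remained to be enrolled at submission, besides anyone then still waiting.

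**The case against.** The strongest reply is that this is a condensed article. The full protocol is not shown, and a repeat safety check before a device is first used may be routine there. Nothing in the article contradicts a re-check. That limits the point but does not remove it: Table 1 is the trial's stated schedule, it lists this checklist as its own row, and it places it only before T0. If a re-check exists, the table should show it.

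The second reply is that a new contraindication is unlikely to go unnoticed. Participants live where staff are available around the clock. The researcher who maintains contact during the wait also follows up positive checklist answers. Case managers complete informant forms at T1. A severe lesion at an electrode site would probably be seen when the electrodes are fixed, although that is after allocation. These routes make an undetected case less likely, and that part of the reply stands. None of them is an eligibility check, and none is tied to randomisation.

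A reader might also infer more than the documents support:
- *That a newly ineligible person is still randomised.* The article says neither that such a person is randomised nor that such a person is withdrawn. The supported statement is that no scheduled step prevents it.
- *That the active-versus-sham comparison is materially diluted.* Statistical analysis treats that comparison as secondary and hypothesis-generating, and the primary CR effect is pooled across stimulation conditions. Any effect of a few such participants would be negligible.
- *That the absence of a data monitoring committee makes this worse.* Such a committee does not screen individuals before allocation, so it has no bearing here.

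**Conclusion.** The point holds as a scheduling gap. The only scheduled tDCS contraindication check falls at least 16 weeks before allocation and first stimulation, and the article describes no step that re-confirms the exclusion in between. A contraindication arising during the wait would come to light only through informal contact or general adverse event reporting.

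The 16-week minimum comes straight from the stated design. The conclusion rests on reading Table 1 as the complete schedule for this checklist; a re-check in the full protocol would reduce the point to a correction of the table. The number of participants affected cannot be derived from the documents. The case for change is participant safety at very low cost, and no claim is made about bias or power.

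**What to change.** Add the existing tDCS checklist to the T1 column of Table 1, completed before allocation, and say so under Trial design and Study population. Any new positive answer should be resolved before randomisation by the route Study population already sets out. No new instrument or criterion is needed.

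The sponsor should also state what follows for a participant found ineligible for tDCS at T1: whether that person still receives CR, and whether T2 and T3 data are collected and enter the pooled primary CR analysis. Two statements in the article make this necessary. Trial design says that all participants are able to receive the intervention, and the planned models include stimulation condition as a between-subject variable, which a person who is not randomised would lack. Which course to take is for the sponsor to decide.

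The cost is one short form per participant at a visit that already takes place, and possibly a few enrolled participants who are not randomised. If the full protocol already requires a re-check, the only change is to show it in Table 1.
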